## Introduction

 Childhood stroke has a pooled incidence of 2.1 per 100 000 person-years.^1^ Global impact is growing, with a 35% increase in prevalence from 1990 to 2013.^2^ Childhood stroke is associated with high rates of neurological impairment and substantial economic costs.^3
4^ Stroke is eminently treatable but time-critical. Reperfusion therapies, which include intravenous thrombolysis and endovascular clot retrieval (ECR), are established as effective to improve long-term outcomes of adults with acute ischaemic stroke.^5
6^

The catchcry in emergency stroke treatment that *time is brain* is equally applicable to children because failure to save brain results in poorer outcomes.^7^ Survivors of childhood stroke face decades of living with disability and with that comes a significant impact on their families and the broader community. The long-term economic and societal cost of childhood stroke is not well elucidated, with previous US studies reporting the economic impact only up to 5 years from stroke event.^3^

The days of therapeutic nihilism in adult stroke have passed, yet children are still not receiving the benefits of reperfusion therapies, often because of diagnostic delay, sometimes extending beyond 24 hours.^8^ Delays prior to arrival relate to limited awareness of stroke among caregivers,^9^ clinical recognition among paramedics^10^ and emergency physicians,^11^ and poor accuracy and reliability of prehospital decision support tools.^12^ In contrast to adults, in-hospital factors—particularly delayed access to rapid diagnostic imaging in the emergency department (ED)^13^ and poor sensitivity of CT-based imaging for detection of infarction in children with arterial ischaemic stroke (AIS)^14^—are more important contributors to delayed diagnosis than prehospital factors. Therefore, institutional and regional systems of acute care are required to streamline diagnosis and initial treatment of childhood stroke.

In adults with stroke, there has been a move towards tissue-based rather than time-based selection of candidates for reperfusion therapies to salvage viable brain. This approach using advanced brain imaging, which quantifies penumbral tissue destined for infarction if blood-flow is not restored, has led to use of thrombolysis^15
16^ and ECR^17^ in extended time windows beyond 4.5 and 6 hours, respectively. These diagnostic advances have only recently been tested in observational studies in children^18

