### Study setting and procedures

The study is being conducted at eight tertiary paediatric hospitals in Australia and one tertiary paediatric hospital in New Zealand that meet recommended international criteria for primary paediatric stroke centres^28^ from 2020 until 2026. These hospitals include (1) the Royal Children’s (RCH) and (2) the Monash Children’s Hospital (MCH), both in Melbourne, Victoria, Australia, (3) the Sydney Children’s Hospital (SCH), (4) the Children’s Hospital at Westmead (CHW), both in Sydney and (5) the John Hunter Children’s Hospital (JHCH), Newcastle, New South Wales, Australia, (6) the Queensland Children’s Hospital (QCH), Brisbane, Queensland, Australia, (7) the Women’s and Children’s Hospital (WCH), Adelaide, South Australia, (8) the Perth Children’s Hospital (PCH), Perth, Western Australia and (9) the Starship Children’s Hospital (StCH), Te Toka Tumai, Auckland, New Zealand (online supplemental e-Table 1).

The Code Stroke protocols tailored to local resources are being primarily followed in the EDs but also target inpatients with conditions associated with a risk of stroke (eg, children with cardiac disease). The EDs are members of the PREDICT research network.^33^ These hospitals will partner with adult comprehensive stroke centres to develop PACS protocols tailored to each hospital. Common elements will include (1) clinical criteria that trigger activation of the Code Stroke protocol, (2) clinical assessment which includes the pedNIHSS, (3) baseline bloods, (4) agreed on minimum imaging dataset (for MRI axial T1, T2, FLAIR, diffusion weighted imaging, apparent diffusion coefficient, susceptibility weighted imaging and time of flight MR angiography sequences and inclusion of CT angiography in CT based protocols) and (5) eligibility for thrombolysis. These elements align with the national childhood stroke guideline. There will be resource-related protocol variability in (1) type of initial imaging (CT vs MRI), (2) use of perfusion imaging and (3) ECR (case-by-case discussion for children presenting in the 6–24 hours’ time-window, and (4) whether this is performed on site at the paediatric hospital or at an adult comprehensive stroke centre.

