### Study participants, inclusion and exclusion criteria

During the pre-implementation phase, from 2015 to 2017, children aged 1 month to 18 years with radiologically confirmed stroke will be retrospectively identified from ICD10 principal diagnosis codes for stroke and then medical record review.

During the Code Stroke protocol development and post implementation phases from 2018 to 2026, children aged 1 month to less than 18 years of age with symptoms of less than 24 hours duration that are suspicious for stroke (also referred to as brain attacks)^34^ will be eligible for recruitment to the PACS study. Symptoms include altered consciousness; focal face arm or leg weakness; dysarthria; dysphagia; sensory disturbance; visual disturbance; limb incoordination/ataxia; visual/sensory neglect; pupillary abnormality; severe headache with associated focal neurology and seizure(s) with associated focal neurology^28^ (figure 1). Patients will be categorised into two final diagnostic groups: stroke or mimics, based on presence or absence of acute ischaemic or haemorrhagic infarction on brain imaging. Stroke will be further sub-categorised into AIS or haemorrhagic stroke (HS) as adjudicated by a paediatric radiologist. Children with acute neurological symptoms that are not relevant for stroke will be excluded from the study.

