### Interventions

#### Code Stroke protocol development and implementation (all PACS sites)

A Code Stroke protocol^35
36^ is a hospital-based protocol and multidisciplinary emergency response system designed to standardise initial clinical assessment and urgent imaging of children with suspected stroke, informed by evidence-based guidelines.^28
29^ Components along the process of care, which begins on arrival in the ED, include recognition of symptoms associated with stroke^37^ at the time of triage, which leads to activation of Code. This triggers rapid clinical assessment by ED physicians. Neurologists will confirm the presence of neurological signs and assess the severity of symptoms using the paediatric adaptation of the National Institutes of Stroke Severity Scale (pedNIHSS),^38^ and in the context of ischaemic stroke, to screen children for eligibility and contraindications to reperfusion therapies, which includes collection of bloodwork. The clinicians decide the need for and type of brain imaging (CT or MRI) to confirm stroke diagnosis. Imaging leads to decisions about reperfusion therapies for ischaemic stroke or neurosurgical intervention for HS. An example of a Code Stroke pathway is presented in figure 1.

The five tertiary paediatric hospitals without established institutional Code Stroke protocols at commencement of the study will develop and implement the protocols through establishment of multidisciplinary working groups including—but not limited to—paediatric ED physicians, neurologists, neurosurgeons, radiologists, stroke research nurses, anaesthetists, intensivists, haematologists and neuro-interventional radiologists. Current practice will be evaluated through engagement of these stakeholders, and site-specific analysis of barriers and enablers to improving stroke diagnosis will be identified, drawing on previous conceptual modelling using Value Focused Process Engineering to map the process of care in children with suspected stroke.^39^

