## Data collection

### Pre-implementation and pre-protocol development phase

All sites will retrospectively collect data for confirmed strokes by case record review from 2015 to 2017, using the ICD-10 codes: I61.0–I61.6, I61.8, I61.9, I62.9, I63.0–I63.6, I63.8, I63.9, I64.0 and G45, for the primary aim of determining time to diagnosis prior to implementation of Code Stroke protocols across study sites (table 1).^40
41^

**Table 1 T1:** Data to be collected

Variables	Pre-implementation (2015–2017) confirmed stroke	Post implementation phase (2018 onwards) stroke	Post implementation phase (2018 onwards) mimics
Demographics	✓	✓	✓
Prehospital care*	✓	✓	✓
Presenting clinical features	✓	✓	✓
pedNIHSS (baseline, 24 and 48 hours)	✓†	✓	✓‡
EMS call taker and paramedic coded diagnoses*	✓	✓	✓
Sensitivity of ED physician diagnosis		✓	✓
Time to diagnosis§	✓	✓	✓
Timelines of care (pre- and post-arrival)	✓	✓	✓
Length of stay, acute hospital and inpatient rehabilitation	✓	✓	✓¶
Follow-up phone call following ED discharge for mimics to confirm no change in diagnosis		✓	✓
Rates of reperfusion therapy use (t-PA and ECR)	✓	✓	
Reperfusion therapy related serious adverse events	✓	✓	
Neurological outcomes: Outcomes: (PSOM and mRS) at discharge 7, 30 and 90 days. mRS at 30 and 90 days	✓	✓	
Child Health Utility (CHU-9D)		✓	
Costs of childhood stroke, using hospital/Medicare linked services health utilisation cost data		✓	

* For the subgroups of children transported to ED by ambulance.

† Paediatric version National Institutes of Health Stroke Scale (pedNIHSS) and Paediatric Stroke Outcome Measures (PSOM) may be derived retrospectively in some (but not all) patients from clinical assessment notes and should be collected if applicable.

‡ Only at baseline.

§ Time to diagnosis will be collected for all children presenting to the emergency department, regardless of mode of arrival and for inpatients where a Code Stroke is activated.

¶ Only if admitted.

ECR, endovascular clot retrieval; ED, emergency department; EMS, emergency medical services; mRS, modified Rankin score; tPA, tissue plasminogen activator.

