## Discussion

More than half of children who experience a stroke have long-term impairments impacting motor, cognitive, language, behaviour and social functions.^7^ The overall goal of the PACS study is to improve survival outcomes for Australian and New Zealand children with stroke through the development and implementation of childhood Code Stroke protocols, targeting key steps along the process of care.^39^ The primary objective is to bring childhood stroke diagnosis into the 4.5-hour time-window for reperfusion therapies and, by extension, to narrow the gap between adults and children in accessing life-changing treatments.

There is limited reporting of the efficacy and safety of reperfusion therapies in children because randomised controlled trials have excluded patients <18 years^5
6^ and stand-alone paediatric trials are not thought to be feasible following the failed international TIPS trial.^47^ Consensus-based childhood stroke guidelines allow for reperfusion therapies but there is a strong imperative to collect real-world safety and efficacy data for these interventions.^28
29^

The diagnostic utility of automated perfusion imaging to quantify brain at risk of infarction will be prospectively evaluated in the PACS study, which is aligned with the shift in adults towards adopting tissue-based (volume of brain as quantified by perfusion imaging), rather than time-based decisions about use of reperfusion therapies. This approach is more scientifically valid in children, given the more varied causes, which differ from adults^48^ and delays to stroke diagnosis.

Testing the utility of clinical decision support tools will inform paramedic clinical practice guidelines. The PACS study will also, for the first time, generate a national Australian childhood stroke dataset demonstrating the impact of reperfusion therapies on functional outcomes, which will be benchmarked against adults with stroke using the AuSCR registry.

The health economic analyses will generate data about the economic burden of childhood stroke and the associated loss of QALYs in Australian children, to allow more targeted use of health resources. Knowledge gains from the study will be incorporated in the Stroke Foundation of Australia living guidelines for stroke.^49^

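### Table 1 collects reperfusion use and its serious adverse events by final diagnosis, not by treatment received, so a treated child finally classed as a mimic is missing from the safety data it specifies

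*Protocol article*

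**What the plan says.** Table 1 (section on the pre-implementation and pre-protocol development phase) has three columns: pre-implementation stroke, post implementation stroke, and post implementation mimics. The rows for reperfusion use and for "Reperfusion therapy related serious adverse events" are ticked in both stroke columns and blank for mimics. The blanks look deliberate, because other rows carry entries tailored to mimics: pedNIHSS at baseline only, and length of stay only if admitted. The functional outcome row (PSOM and mRS) is also blank for mimics.

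The section on study participants and eligibility criteria assigns the final diagnostic group: "stroke or mimics, based on presence or absence of acute ischaemic or haemorrhagic infarction on brain imaging". Treatment received plays no part in that assignment.

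Three other places bear on whether a treated child can end up as a mimic:
- The section on Code Stroke protocol development states that "Imaging leads to decisions about reperfusion therapies for ischaemic stroke or neurosurgical intervention for HS", so imaging comes first.
- The section on study setting and procedures lets the first imaging modality (CT or MRI) vary with site resources. It also puts CT angiography in CT-based protocols and MR angiography in the MRI dataset.
- The Introduction names "poor sensitivity of CT-based imaging for detection of infarction in children with arterial ischaemic stroke (AIS") among the in-hospital causes of late diagnosis.

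The Discussion says that "there is a strong imperative to collect real-world safety and efficacy data for these interventions". The section on the protocol development and post implementation phases refers the full variable list to online supplemental e-Table 2, which is not shown.

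**The concern.** A safety set for a treatment should be defined by who received the treatment. Table 1 defines it by final diagnosis, which may be settled only after treatment. A child treated on clinical and early imaging grounds who never shows an infarct moves to the mimic column, where neither the treatment nor a related serious adverse event is a listed item. The other mimic rows would give only indirect traces of harm, such as length of stay if admitted or the follow-up call, since the later pedNIHSS scores and the functional outcomes are not collected for mimics either.

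This is selection on an outcome. The children lost are those treated without a confirmed infarct, a group that matters to anyone judging a pathway meant to speed diagnosis and widen access to reperfusion. More reperfusion use is the first secondary aim, and the Discussion gives real-world safety data as a reason to collect evidence, so the omission works against the study's own purpose.

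**Working it through.** The point concerns which data are collected, so the plan has no power or sample-size figure to reproduce. The check sets the sections side by side and then gauges the scale.

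**Can a treated child be classed as a mimic?**
1. The treatment decision follows imaging (Code Stroke protocol development). The article does not say that an infarct must be visible at that moment.
2. The first imaging may be CT (Study setting and procedures), which the Introduction calls poorly sensitive for infarction in childhood AIS.
3. The final group depends on infarction on brain imaging, not on the first scan alone. A stroke missed on CT and seen on a later scan is classed as stroke, and its treatment and adverse events are collected.
4. What remains is a child who is treated and has no infarct on any scan. The article's wording permits this, and Table 1 then lists neither the treatment nor the related event.

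**Scale.** Inputs from the section on sample size and power calculations: 326 children with suspected stroke in the protocol development and prospective phases, and 98 confirmed strokes per phase.
- Expected mimics: 326 − 98 = 228, or 228/326 = 69.9%. At exactly one stroke in three, 326/3 ≈ 109 strokes and 326 − 109 = 217 mimics.
- The article gives no rate p at which mimics are treated, so p is assumed. Expected treated mimics = 228 × p. Chance of at least one = 1 − (1 − p)^228.
- The article gives no treatment rate among strokes either. At an assumed 10% to 14%, treated strokes number 98 × 0.10 = 9.8 to 98 × 0.14 = 13.7.
- Share of all treated children missing = treated mimics / (treated mimics + treated strokes). For p = 1%: 2.28/(2.28 + 13.72) = 14% to 2.28/(2.28 + 9.8) = 19%.

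| Assumed p | Expected treated mimics | Chance of at least one | Share of treated children missing |
|---|---|---|---|
| 0.5% | 1.1 | 68% | 8–10% |
| 1% | 2.3 | 90% | 14–19% |
| 2% | 4.6 | 99% | 25–32% |
| 5% | 11.4 | over 99.9% | 45–54% |

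With 217 mimics the expected counts are 1.1, 2.2, 4.3 and 10.9. Both rates are assumptions, so the table shows only that a handful of children would be a noticeable part of a small treated group. The mimic count may also include children who were never imaged (the study procedure section provides a six-week call for suspected strokes without imaging). They could not reach treatment by the described pathway, so 228 overstates the number at risk.

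**The case against.** The strongest reply is that Table 1 summarises a longer list in a journal article. e-Table 2, or safety reporting rules in the full protocol, may record reperfusion use and serious adverse events for every child. That stands as a limit: a reader might infer that harm to treated mimics goes unrecorded, but the article shows only that Table 1 does not list it. It does not dispose of the point. Table 1 states positively what is collected for mimics, and if e-Table 2 collects more, the two need aligning.

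Second, imaging with angiography precedes treatment, so treated mimics should be uncommon. That also stands. A reader might go further and call harm to treated mimics the main risk of a faster pathway. No section says so, and none gives a rate.

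Third, with about 70% of suspected strokes expected to be mimics, a reader might infer that reperfusion safety is uncollected in over two thirds of the prospective cohort. That does not follow: an untreated child has no reperfusion safety data to lose. Only treated mimics count.

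Fourth, the blanks match the listed outcomes. Reperfusion use is analysed as for the primary outcome, which concerns children with stroke, and reperfusion safety is not a listed outcome in the data analysis plan. This explains the blanks. However, Table 1 does collect reperfusion-related serious adverse events, so some account of safety is intended, and it should cover everyone exposed.

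Last, a reader might infer that the primary outcome loses its best results, namely children reperfused before any infarct forms, and want them reclassified as strokes. The article gives no frequency for such children, and it defines time to diagnosis by radiological confirmation of infarction or haemorrhage. The pre-implementation cases are radiologically confirmed strokes found retrospectively. Reclassification would make the case definition depend on a treatment the study aims to increase, and would make it differ between phases.

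**Conclusion.** The point holds for data capture. As Table 1 specifies them, reperfusion use and related serious adverse events are collected according to final diagnosis, and a treated child without infarct is left out. The size is unknown and probably small: about 1 to 5 children if 0.5% to 2% of 228 mimics were treated, which is an assumption. It still matters, because the treated stroke group may itself be only about 10 to 14 children (again assumed) and the omission is selective. The conclusion is conditional on e-Table 2 not already capturing these children. It does not touch the primary outcome, the sample size or the power.

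**What to change.** - Tick both Table 1 rows, reperfusion use and reperfusion-related serious adverse events, for all prospectively recruited children, whatever their final diagnosis.
- Define the reperfusion safety set as every child given thrombolysis or ECR. Report the number of treated mimics and their serious adverse events separately. This will be descriptive and limited to the prospective phases, since the pre-implementation phase includes confirmed strokes only.
- Check e-Table 2 and the database. If they already record these items for mimics, correct Table 1 to match; if not, add them.
- Leave the stroke/mimic definition for the primary outcome unchanged, so that the case definition stays the same in both phases.

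The cost is two database fields and back-filling for the few treated mimics already enrolled. Data collection continues to mid-2026, so the change can still be made while the study is running. It alters no treatment rule.

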### Protocol development and post implementation phases

During this phase, data will be collected for children presenting to the ED with brain attack symptoms relevant for stroke.

For secondary aim (4), in participants with confirmed stroke, the health economic impact will be determined using the Child Health Utility-9D (CHU-9D) as a paediatric generic preference-based measure of health-related quality of life, to allow calculation of quality-adjusted life years (QALYs) in cost-utility analyses.^42^ Data will be entered into a REDCap database (table 1).

For secondary aim (5), the Paediatric Stroke Outcome Measures^40^ and the paediatric version of the modified Rankin Scale^41^ will be derived where possible if data are available for the retrospective patient cohort in the pre-implementation phase, and prospectively collected in the protocol development and post implementation phases.

The full list of data variables collected is detailed in online supplemental e-Table 2.

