**Figure 4 F4:**
[figure not shown]
PACS study outcome measures and analyses. AIS, arterial ischaemic stroke; AuSCR, Australian Clinical Stroke Registry; BASICS, Brain Attack and Stroke in Children Screen; ED, emergency department; EMS, emergency medical services; PACS, Paediatric Acute Code Stroke; ROC, receiver operating characteristic; tPa, tissue plasminogen activator.

Due to the hospital-based nature of the proposed intervention, when powering this study, we have taken appropriate care of the hierarchical nature of the data, where individual patients are clustered within the treating hospitals. It is therefore appropriate to anticipate the presence of a design effect (expressed through the value of the intraclass correlation coefficient), as would have to be done in the situation of cluster-randomised studies. In addition, different hospitals will be able to recruit different numbers of patients, thus there will be a variation of cluster sizes.

Nine hospitals are participating in the study. At the time of receiving grant funding in July 2020, seven hospitals had agreed to participate in the study. Based on this consideration, assuming the settings of alpha=0.05, the intraclass correlation coefficient of 0.05 (corresponding to a small-to-medium hospital-specific effect) and the coefficient of variation of hospital-based cluster sizes of 0.5 (medium-to-high level of variation) with at least seven hospitals, recruiting the 98 patients with radiologically confirmed diagnosis of stroke in the pre-PACS implementation phase and 98 patients in the post-PACS protocol implementation stage (on average 14 patients per hospital for both pre-implementation and post implementation stages), will yield 80% power to detect a change from 0.15 to 0.40 in proportion of children diagnosed within 4.5 hours of symptom onset.

In addition, this sample size will be sufficient for further validation and continuous updating of the BASICS tool in order to further improve its predictive capacity (as the total number of screened patients is expected to be at least three times the number of confirmed strokes).^30
31^

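### Inpatient strokes are timed only if a Code Stroke is activated, while pre-phase strokes enter by diagnosis code, so the inpatient part of the primary comparison is not like with like

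*Protocol article*

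**What the plan says.** All references are to the protocol article.

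- **Timing rule.** The footnote to the time-to-diagnosis row of Table 1 covers every child presenting to the ED, "regardless of mode of arrival and for inpatients where a Code Stroke is activated".
- **Target of the intervention.** Under Study setting and procedures, the protocols are followed mainly in the EDs "but also target inpatients with conditions associated with a risk of stroke".
- **Pre-phase entry (2015 to 2017).** Under Study participants, children with confirmed stroke are "retrospectively identified from ICD10 principal diagnosis codes for stroke and then medical record review". No ED presentation, activation or limit on symptom duration is required.
- **Post-phase entry (2018 onwards).** The same section requires suspicious symptoms lasting under 24 hours. The later section on the protocol development and post implementation phases says "data will be collected for children presenting to the ED with brain attack symptoms relevant for stroke" and does not mention inpatients.
- **Post-phase screening.** The study procedure section relies on ED triage and discharge lists, triage alerts and notification by on-call neurology. It describes no search of the wards.
- **Primary model.** Under Data analysis plan, phase is the only fixed effect and hospital is a random effect. There is no term for ED versus inpatient setting.

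**The concern.** Activation is the first step of the intervention under test. If an inpatient's time is recorded only when that step occurred, inpatient strokes for which no code was called are missing from the post-phase denominator. Those are the cases the intervention did not reach, and they are likely to be diagnosed late. The pre-phase has no matching exclusion, or else has almost no inpatients at all.

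Two further differences in entry accompany this. A principal-diagnosis search can miss a stroke that occurs during an admission for something else. The 24-hour limit, applied only after implementation, removes late presenters who would count as failures in the pre-phase.

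The primary result is a plain contrast of proportions between phases, so a change in who is counted appears as a change in performance. Times that were never collected cannot be restored by an analysis plan.

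**Working it through.** **1. The plan's own figure.** The inputs, from Sample size and power calculations, are "assuming the settings of alpha=0.05, the intraclass correlation coefficient of 0.05", "the coefficient of variation of hospital-based cluster sizes of 0.5 (medium-to-high level of variation) with at least seven hospitals" and "on average 14 patients per hospital for both pre-implementation and post implementation stages". The claim is that 98 strokes per phase "will yield 80% power to detect a change from 0.15 to 0.40 in proportion of children diagnosed within 4.5 hours". Sidedness is not stated; two-sided is assumed.

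- Design effect = 1 + ((1 + CV²)m − 1) × ICC = 1 + (1.25 × 14 − 1) × 0.05 = 1.825.
- Effective n per phase = 98 / 1.825 = 53.7.
- Power for 0.15 against 0.40: 83.7% (pooled normal), 77.5% (continuity-corrected), 79.2% (noncentral t with 2 × (7 − 1) = 12 degrees of freedom).

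The stated 80% is reproduced. The power calculation is not at fault.

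**2. Two readings of the footnote, with no true effect.** The article gives no inpatient share *f*, inpatient in-time rate or activation rate. All are assumed below. The ED in-time rate is set at the plan's 15% in both phases.

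*Reading (a): all coded inpatients count before, only activated ones after.* Let *q* be the inpatient in-time rate (15% or 30%). Activation is 90% for inpatients diagnosed in time and *b* (10%, 30% or 50%) for the others.

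- Pre = 0.15(1 − f) + f·q.
- Post = [0.15(1 − f) + 0.9·f·q] / [(1 − f) + f(0.9q + b(1 − q))].
- Smallest rise (f = 0.1, q = 0.30, b = 0.5): pre 0.165; post = 0.162 / 0.962 = 0.168; rise 0.3 points.
- Largest rise (f = 0.3, q = 0.15, b = 0.1): pre 0.150; post = 0.1455 / 0.766 = 0.190; rise 4.0 points.

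*Reading (b): the footnote applies in both phases, so the pre-phase has almost no inpatients.* Let *p* be the in-time rate among activated inpatients, and *f* their share of post-phase strokes. Pre = 0.15 and Post = 0.15(1 − f) + f·p. The last column is the chance of a significant increase (pooled z, effective n 53.7 per phase), nominally 2.5%.

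| f | p | Post | Rise (points) | False significance |
|---|---|---|---|---|
| 0.1 | 0.3 | 0.165 | 1.5 | 4.0% |
| 0.1 | 0.7 | 0.205 | 5.5 | 11.2% |
| 0.2 | 0.5 | 0.220 | 7.0 | 15.1% |
| 0.3 | 0.3 | 0.195 | 4.5 | 8.9% |
| 0.3 | 0.7 | 0.315 | 16.5 | 52.6% |

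**3. Cost of an ED-only primary set.** Remove a share *f* from 98 in each phase, keeping 7 hospitals, ICC 0.05 and CV 0.5.

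| f | n per phase | Mean per hospital | Design effect | Effective n | Power (pooled) |
|---|---|---|---|---|---|
| 0 | 98 | 14.0 | 1.825 | 53.7 | 83.7% |
| 0.1 | 88.2 | 12.6 | 1.7375 | 50.8 | 81.5% |
| 0.2 | 78.4 | 11.2 | 1.65 | 47.5 | 78.8% |
| 0.3 | 68.6 | 9.8 | 1.5625 | 43.9 | 75.5% |

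**The case against.** The strongest reply is that the footnote annotates a data-collection table and does not define an analysis set. The outcome is stated over children with stroke, and analysis sets may be defined in a document not shown. That is fair as far as it goes, but the footnote governs which times are collected, and no later document can analyse the others.

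A second reply is that inpatients may be few. The protocols are followed mainly in the EDs, and one section describes post-phase collection for ED presentations only. If that section governs, the inpatient share is near zero and so is this bias. This stands as a reason not to assume a large share. It is also a contradiction with the footnote that has to be resolved.

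A third reply is that the Discussion already concedes bias from mixing retrospective and prospective data. It does so in general terms, without naming the activation condition or the different entry rules.

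Three stronger inferences are tempting, and the article does not support them:

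- *The whole post-phase is selected on having received the intervention.* It is not. ED children count with or without activation, and ED lists are reviewed even where stroke was not suspected. Only post-phase inpatients are affected.
- *Inpatient strokes recognised late are excluded.* The footnote requires activation, not prompt activation. A late-activated inpatient who meets the 24-hour limit counts as a failure at 4.5 hours.
- *A large false-positive rate has been demonstrated.* The high figures need reading (b) together with a large share of quickly diagnosed inpatients. The article states neither.

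**Conclusion.** The point holds for the inpatient part of the comparison. As written, inpatients enter the two phases under different rules on either reading of the footnote, and the primary model has no term that could absorb the difference. The two readings are alternatives: the footnote cannot both remove pre-phase inpatients and leave coded non-ED admissions in.

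The likely direction is toward benefit. The size is unknown. The 0.3 to 4 points of reading (a) and the 1.5 to 16.5 points of reading (b) are illustrations over assumed ranges, as is the 4% to 53% false significance attached to the latter. At the lower end the bias is negligible beside the planned 25 points; at the upper end it could produce a significant result alone. The article gives no basis for choosing between them. It also does not say whether any site ran a code before 2018, which bears on how empty the pre-phase would be under reading (b).

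**What to change.** Use one entry rule in both phases.

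1. Restrict the primary analysis set, before and after, to confirmed strokes presenting through the ED, with the same symptom-duration limit in both.
2. Reconcile the Table 1 footnote, the setting section and the post-phase data-collection section on whether inpatients are in the study and which times are recorded for them.
3. Report inpatient-onset stroke separately in both phases, regardless of activation.
4. Run the existing ICD-10 principal-code search for the post years too, so that strokes missed by prospective screening enter the denominator. A search in any diagnosis position would find more in-hospital strokes, but it is optional and is new record review in both periods.

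**Cost.** There is some extra record review, and it should be confirmed that approvals and consent arrangements cover cases found this way. The primary set also shrinks: at an assumed 10% to 30% inpatient share in each phase, power falls from 83.7% to between 81.5% and 75.5%. Because inpatients are a stated target of the protocols, an ED-only primary set also narrows the question, which is why the separate inpatient report is needed. Data collection runs to mid-2026, so the rule should be settled while times can still be collected.
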